## MATERIAL AND METHOD

### Study Design

This is a clinical trial protocol, controlled, randomized, single-blind with two groups, an allocation ratio of 1:1, and a hypothesis of superiority that will be carried out with patients admitted to the adult Intensive Care Unit (ICU) of the University Hospital Onofre Lopes (HUOL) with the clinical diagnosis of acute myocardial infarction. Figure 1 represents the follow-up flowchart of the study according to CONSORT (Consolidated Standards of Reporting Trials) (49). Figure 2 presents the flowchart with the main stages of the study.

[figure not shown]

**Fig. 1** – Study flowchart according to the Consolidated Standards of Reporting Trials (CONSORT).

## **Study design**

[figure not shown]

**Fig. 2** – Flowchart with specification of the evaluations and interventions carried out.

## **Study setting**

This study will be developed at the University Hospital Onofre Lopes (HUOL), in the adult Intensive Care Unit (ICU), and in the clinical wards, located in the city of Natal/Rio Grande do Norte.

## **Participants**

The patients included in the study will be patients admitted to the adult ICU at HUOL with a confirmed clinical diagnosis of AMI (ECG and cardiac enzymes) with or without ST elevation and uncomplicated (Killip I or II), undergoing percutaneous coronary intervention (PCI) with success (Timi flow 2 or 3), aged between 18 years and 70 years and of both sexes, classified as low risk (EF>50%, absence of ventricular dysrhythmias, absence of clinical depression and ischemic signs or symptoms after the procedure) according to the American Association of Cardiovascular and Pulmonary Rehabilitation (AACPR) risk classification (50) and ability to provide informed consent. Exclusion criteria determined include the presence of musculoskeletal disorders that prevent the performance of exercises, signs, and symptoms of cardiac ischemia or decompensation, atrial or ventricular arrhythmias, and diagnosed pulmonary diseases (e.g., pulmonary hypertension, COPD, among others).

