### **Secondary objectives**

- To assess the variation in functional capacity by measuring cardiorespiratory fitness after in-hospital CR, using maximum VO2 (maximum oxygen consumption) as a result measure;
- To analyze the dose of aerobic training provided to patients in in-hospital CR and its impact on the outcome of functional capacity;
- Relate the standard method of measuring VO2, the cardiopulmonary test, to a submaximal evaluation method, the 30s sit-to-stand test, evaluating its validity and reproducibility;
- Observe the influence of early CR on the morphological parameters of ventricular remodeling through nuclear magnetic resonance (NMR);
- Investigate heart rate variability after early cardiac rehabilitation.
- Identify the rate of adverse events and the safety level of the protocol evaluated in this clinical trial;

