## **Sampling and Recruitment**

Participants will be recruited from the adult intensive care unit (ICU) shortly after admission for a percutaneous coronary intervention (PCI) procedure. The sample size was calculated using the OpenEpi software through the mean difference found in a previous study (29) with in-hospital CR for analysis of maximum oxygen consumption (VO2). A number of 7 participants per group was verified with a total of 14 for the sample considering a significance level of 5%, and a statistical power of 80%. Adding a 30% rate for possible losses during the study, we chose to recruit 12 participants per group for a total sample size of 24 patients. The patients included in the study will be patients admitted to the adult ICU at HUOL with a confirmed clinical diagnosis of AMI (ECG and cardiac enzymes) with or without ST elevation and uncomplicated (Killip I or II), undergoing percutaneous coronary intervention (PCI) with success (Timi flow 2 or 3), aged between 18 years and 70 years and of both sexes, classified as low risk (EF>50%, absence of ventricular dysrhythmias, absence of clinical depression and ischemic signs or symptoms after the procedure) according to the American Association of Cardiovascular and Pulmonary Rehabilitation (AACPR) risk classification (50) and ability to provide informed consent. Exclusion criteria determined include the presence of musculoskeletal disorders that prevent the performance of exercises, signs, and symptoms of cardiac ischemia or decompensation, atrial or ventricular arrhythmias, and diagnosed pulmonary diseases (e.g., pulmonary hypertension, COPD, among others).

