### **Early cardiac rehabilitation program**

The early cardiac rehabilitation (CR) program based on physical exercise will be carried out in 3 steps (Step 1 - Functional mobilization; Step 2 - Early cardiac rehabilitation; Step 3 - Continued cardiac rehabilitation).

In step 1 of early mobilization, all patients in the control and intervention groups, after 8 hours of clinical stability (absence of ischemic signs and symptoms) will perform mobility increment exercises to ensure functional mobility until discharge from the ICU, as per step 1 of the in-hospital CR protocol in (Appendix B). After ensuring functional mobility, patients will be randomized to control or intervention groups. Both groups will perform steps 1 to STEP 3 of the early CR protocol, with the physical activity is a free-demand ambulation in addition to standardized drug treatment, however, only the intervention group will proceed to STEP 4 of steps 1 and steps 2 and 3 from early and continued cardiac rehabilitation.

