### Cardiohemodinamic safety of early cardiac rehabilitation

The safety of the institutional protocol tested in this trial will occur through notifications

of adverse events during and after the CR sessions provided to patients in the intervention group. We will report adverse events session by session, listing the main ones: arrhythmias, chest pain, borg>13, drop in systolic blood pressure (SBP) above 10 mmHg, and cardiorespiratory arrest. Other events not previously listed will also be recorded in the patient follow-up and evaluation form as per Appendix A.

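### Adverse events in STEPS 1-3, which come before randomisation, are left out of the safety rate for patients never randomised and for those later allocated to control

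*Protocol*

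**What the plan says.** All references are to the Protocol.

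- **Recruitment** (Sampling and Recruitment): "Participants will be recruited from the adult intensive care unit (ICU) shortly after admission for a percutaneous coronary intervention (PCI) procedure".
- **Exclusions** (Participants, repeated under Sampling and Recruitment): musculoskeletal disorders that prevent exercise, then "signs, and symptoms of cardiac ischemia or decompensation, atrial or ventricular arrhythmias, and diagnosed pulmonary diseases". The text does not say when these are judged.
- **Order of exercise and allocation** (Early cardiac rehabilitation program): all patients begin step 1 after 8 hours of stability. Then: "After ensuring functional mobility, patients will be randomized to control or intervention groups". Both groups do STEPS 1 to 3, and "only the intervention group will proceed to STEP 4 of steps 1 and steps 2 and 3".
- **Sit-to-stand test**: the same section has it assessed before randomisation, and Appendix B lists it as the muscular endurance item of STEP 3.
- **Conditions for progress** (Appendix B): STEP 1 requires more than 8 hours without signs of ischaemia or decompensation. STEP 3 requires that the earlier conditions still hold.
- **Safety count** (Cardiohemodinamic safety of early cardiac rehabilitation): "adverse events during and after the CR sessions provided to patients in the intervention group", the main ones being "arrhythmias, chest pain, borg>13, drop in systolic blood pressure (SBP) above 10 mmHg, and cardiorespiratory arrest".
- **Objectives**: the primary objective names safety as well as efficacy. A secondary objective is to "Identify the rate of adverse events and the safety level of the protocol evaluated in this clinical trial".

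**The concern.** The exercise protocol starts at STEP 1, but the population in which its safety is counted exists only after STEP 3. Two sets of early sessions have no place in the planned rate: those of patients who start and are never randomised, and those of patients who start and are later allocated to control.

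The first set matters more, because those patients may be missing on account of the outcome. Chest pain or an arrhythmia in STEP 1 or 2 can mean that the conditions for STEP 3 are not met, so the patient does not reach the sit-to-stand test or randomisation. The second set is lost by chance allocation, which costs information but does not select on the event.

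The Abstract describes the intervention by its early start, and the Introduction names the safe time to begin as a gap in knowledge. The sessions closest to the 8-hour mark are the ones the counting rule treats worst.

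**Working it through.** **1. Where randomisation falls.** The sit-to-stand test precedes randomisation and belongs to STEP 3. The groups first differ at STEP 4. Randomisation therefore lies between STEP 3 and STEP 4. The test's own section puts its first performance at ICU discharge, which does not move randomisation any earlier.

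**2. Share of the programme before randomisation.** Doses per STEP are from Appendix B.

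- The plan's own totals reproduce: ICU, STEPS 1-4: 10 + 20 + 30 + 30 = 90 MET-min. Ward, STEPS 5-8: 45 + 45 + 60 + 60 = 210. In hospital: 90 + 210 = 300.
- STEPS 1-3: 10 + 20 + 30 = 60 MET-min.
- Shares: 60/90 = 67% of the ICU target, 60/300 = 20% of the in-hospital total, and 3/8 = 37.5% of the STEPS.

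**3. Who is counted in STEPS 1-3.** The target is 12 per group, 24 in total. At least 24 patients do STEPS 1-3, and the rule admits at most 12 of them. With no events in n patients, the exact two-sided 95% upper limit is 1 − 0.025^(1/n):

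- n = 12: 26.5%
- n = 24: 14.2%

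With 12 patients, a single event moves the rate from 0% to 1/12 = 8.3% (exact 95% CI 0.2% to 38.5%). One uncounted event is therefore not negligible.

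**4. Possible size of the understatement.** The Protocol gives no event rate, so the per-session risk p is an assumption, shown over a range. Further assumptions are one session per STEP, constant and independent risk, and, as the extreme case, that every STEP 1-3 event prevents randomisation. The risk over k sessions is 1 − (1 − p)^k. In this extreme case the planned rate reflects only STEPS 4-8 (k = 5), against the full k = 8.

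| p per session | Risk in STEPS 1-3 | Risk in STEPS 1-8 | Rate as counted | Relative shortfall | Uncounted events per 24 starters |
|---|---|---|---|---|---|
| 0.5% | 1.5% | 3.9% | 2.5% | 37% | 0.4 |
| 1% | 3.0% | 7.7% | 4.9% | 37% | 0.7 |
| 2% | 5.9% | 14.9% | 9.6% | 36% | 1.4 |
| 5% | 14.3% | 33.7% | 22.6% | 33% | 3.4 |

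At the other extreme, where no early event prevents randomisation, the systematic shortfall is zero and only the control patients' sessions are lost. The truth lies between these ends, and the document does not allow it to be placed more closely.

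**The case against.** Several points can fairly be made for the plan.

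- **Early events are not all lost.** Appendix A has event boxes from Session 1, so they can be captured for patients later allocated to intervention. This stands. It does not help patients who are never randomised or who become controls, because the counting rule omits them whatever the form records.
- **Eligibility looks like a baseline check.** Recruitment is shortly after admission, and the inclusion criteria require freedom from ischaemic signs after the procedure. This is the more natural reading. The STEP conditions in Appendix B can still stop a patient short of randomisation, and the Protocol does not say where such a patient's event is counted.
- **Flow figures and analysis plan.** The CONSORT flowchart is not reproduced in the text and may show patients who start but are not randomised. A separate analysis plan may define safety populations. Neither removes the rule that the Protocol itself states.

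A reader might also infer more than the text supports:

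- **That the exclusions and the safety outcome are the same events.** Of the five listed safety events, only arrhythmia and chest pain (as an ischaemic symptom) clearly overlap. Borg above 13 and a fall in systolic pressure are not exclusions, and cardiorespiratory arrest is not named as one.
- **That an early event triggers a second eligibility check, or that patients could be removed after randomisation.** The Protocol describes neither.
- **That the comparison between arms is biased.** Both arms complete STEPS 1-3, and the randomised contrast begins at STEP 4, so it is not affected.

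**Conclusion.** The point holds as a defect in the stated counting rule for safety. The planned adverse event rate omits STEP 1-3 events in patients who start but are not randomised and in those later allocated to control. This covers 3 of 8 in-hospital STEPS, 60 of the 90 MET-min ICU target and 60 of the 300 MET-min in-hospital total.

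Losing the control patients' sessions costs precision. Losing patients whose event kept them from randomisation can only understate the early-phase rate. The size of that understatement is unknown. Under the assumptions above it runs from nothing to about a third or slightly more of the eight-STEP risk.

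The conclusion rests on reading randomisation as following STEP 3, which two separate statements support, and on taking the restriction to the intervention group as written. It concerns the descriptive safety rate, which serves both the primary objective and a secondary one, and not the efficacy comparison. It should be corrected.

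**What to change.** In the cardiohemodynamic safety section, count and report adverse events from the first STEP 1 session in every patient who starts it, using the Appendix A form. Present two sets, each with its own denominator: pre-randomisation events among all starters, and post-randomisation events by arm. They should not be pooled, because control patients do not go on to STEP 4 and exposure therefore differs.

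Report how many patients started STEP 1 but were not randomised, with reasons. Under Participants and under Sampling and Recruitment, state that eligibility is judged before the first STEP 1 session. None of this alters the conditions for exercising or progressing.

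The cost is Protocol wording and, if the flow diagram does not already have it, one more line there. Appendix A already provides event boxes from Session 1; it must be completed for all starters. The reported rate may look slightly less favourable. In return, the early-phase estimate rests on at least 24 patients and not on 12.

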## **Sampling and Recruitment**

Participants will be recruited from the adult intensive care unit (ICU) shortly after admission for a percutaneous coronary intervention (PCI) procedure. The sample size was calculated using the OpenEpi software through the mean difference found in a previous study (29) with in-hospital CR for analysis of maximum oxygen consumption (VO2). A number of 7 participants per group was verified with a total of 14 for the sample considering a significance level of 5%, and a statistical power of 80%. Adding a 30% rate for possible losses during the study, we chose to recruit 12 participants per group for a total sample size of 24 patients. The patients included in the study will be patients admitted to the adult ICU at HUOL with a confirmed clinical diagnosis of AMI (ECG and cardiac enzymes) with or without ST elevation and uncomplicated (Killip I or II), undergoing percutaneous coronary intervention (PCI) with success (Timi flow 2 or 3), aged between 18 years and 70 years and of both sexes, classified as low risk (EF>50%, absence of ventricular dysrhythmias, absence of clinical depression and ischemic signs or symptoms after the procedure) according to the American Association of Cardiovascular and Pulmonary Rehabilitation (AACPR) risk classification (50) and ability to provide informed consent. Exclusion criteria determined include the presence of musculoskeletal disorders that prevent the performance of exercises, signs, and symptoms of cardiac ischemia or decompensation, atrial or ventricular arrhythmias, and diagnosed pulmonary diseases (e.g., pulmonary hypertension, COPD, among others).

## **Randomization and blinding**

The randomization sequence will be generated by software available online at [www.randomizer.org](http://www.randomizer.org) by a study collaborator not involved in the processes of collecting or evaluating the results. The software will generate a sequence of uniformly random numbers for 2 groups. The sequence generated by the program will be placed in opaque envelopes and numbered sequentially. The opaque and sealed envelopes will only be under the domain of the researcher responsible for the randomization. Only the collaborators in charge of administering the intervention protocol will be aware of each participant's allocation group. Furthermore, all

outcome assessors will remain blinded during the study to participant allocation.

### **Early cardiac rehabilitation program**

The early cardiac rehabilitation (CR) program based on physical exercise will be carried out in 3 steps (Step 1 - Functional mobilization; Step 2 - Early cardiac rehabilitation; Step 3 - Continued cardiac rehabilitation).

In step 1 of early mobilization, all patients in the control and intervention groups, after 8 hours of clinical stability (absence of ischemic signs and symptoms) will perform mobility increment exercises to ensure functional mobility until discharge from the ICU, as per step 1 of the in-hospital CR protocol in (Appendix B). After ensuring functional mobility, patients will be randomized to control or intervention groups. Both groups will perform steps 1 to STEP 3 of the early CR protocol, with the physical activity is a free-demand ambulation in addition to standardized drug treatment, however, only the intervention group will proceed to STEP 4 of steps 1 and steps 2 and 3 from early and continued cardiac rehabilitation.

In step 2, patients will follow early exercise-based cardiac rehabilitation performed following all prescription parameters (FITT-VP) and safety criteria recommended by ACSM, 2018 (33). The institutional protocol (**Appendix B**) will be performed with a **frequency** of 2 sessions per day, during the entire hospitalization, with an average of 8 to 10 total sessions; Low **intensity** for aerobic training with METs estimated by the subjective perception of effort of BORG between 9 to 12 reaching between 2 to 3 METs and for resistance training with 2 to 3 series of 60% of the maximum repetitions reached in the 30s sit-to-stand test; **Type** of exercises involved will be aerobic training using the cycle ergometer associated with resistance training using the body's own weight with functional sit-to-stand training; Aerobic training **time** ranging from 3 to 20 minutes. The **Volume or Dose** of aerobic training will be measured by calculating the training dose per session and the total dose applied during hospitalization, providing a value in time x intensity (METs) x frequency of accumulated sessions and total number of sessions x time. The structured **progression** in the protocol focuses on the time of aerobic exercise and the number of series of resistance training. The exercise sessions will follow the protocol presented, however, present individualized prescriptions based on tolerance time during aerobic training with a cycle ergometer and resistance training from the maximum number of repetitions reached in the 30s TSL evaluated

individually before randomization.

Before hospital discharge, patients in the intervention group will receive an exercise guidance booklet (Appendix C) to perform step 3 of semi-supervised and continued cardiac rehabilitation with the exercise time reached at the end of in-hospital rehabilitation, frequency of 5 x per week and progression of 5 minutes each week within the first month after hospital discharge, according to tolerance and self-monitoring of intensity through perceived exertion using the Borg scale, maintained between 9 to 12, to ensure light exercise to moderate intensity. In this phase, patients in the intervention group will be monitored weekly by telephone and will receive a diary (Appendix C) to record the time of daily and weekly activity that they must deliver when investigating when they return for reassessment 30 days after hospital discharge.

All patients will be monitored before, during, and after each supervised care session with a frequency meter and pulse oximeter (Model Nonin Onyx 9500, Nonin Medical, USA and Polar H10), which will allow the assessment of heart rate and O2 saturation. Blood pressure will be evaluated before and after the session and during the ICU stay the electrocardiogram will be monitored throughout the exercise. Patients will be instructed to interrupt the exercise in case of malaise (dyspnea, excessive sweating, cyanosis, use of accessory muscles, vertigo, retching), chest pain, or borg greater than 13 for both dyspnea and muscle fatigue.

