## ABSTRACT

Exercise-based cardiac rehabilitation (CR) is a non-drug procedure already clinically incorporated with grade AI recommendation for post-acute myocardial infarction (AMI) patients in the outpatient phase. However, such evidence derives from studies in later phases after the cardiac event. CR in the in-hospital phase and early to the event has grown in the last decade, but its efficacy and safety during the procedure need to be clarified with more robust methodological designs. Thus, this study aims to analyze the effectiveness of a CR protocol based on physical exercises on physical fitness, morphology, and cardiac function, in addition to the cardiohemodynamic safety of inpatients with recent AMI. A controlled and randomized clinical trial will be carried out at the University Hospital Onofre Lopes (HUOL) with a CR protocol based on early physical exercise (>8 hours of clinical stability) of patients with AMI with success in percutaneous coronary intervention (PCI). After randomization, patients will be grouped into GI and CG (intervention and control group). GI will be submitted to a standard low-intensity CR protocol and CG to usual care and mobilization guidelines. Subjects in both groups will undergo the same functional assessments, maximal and submaximal (cardiopulmonary and 30s sit-to-stand tests), cardiac nuclear magnetic resonance, and analysis of heart rate variability. Safety scores and cardiohemodynamic events during rehabilitation will be analyzed. It is expected to observe, at the end of the study, a positive effect of in-hospital CR on cardiac structure and function and its clinical repercussions on the increase of physical fitness, allowing a greater understanding of exercise prescription variables and their physiological responses to predict more therapeutic strategies. efficient and early interventions during the in-hospital rehabilitation process in patients with AMI.

**Keywords:** Early cardiac rehabilitation; physical performance; exercise dose; acute myocardial infarction.

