#### 4.0 Heart morphology after cardiac rehabilitation

Despite the well-documented effects of cardiac rehabilitation in patients with AMI with and without heart failure (HF), there is still uncertainty about this effect on ventricular remodeling. Ventricular remodeling is a broad term used to describe genetic, molecular, neurohumoral, cellular, and interstitial alterations that can culminate in changes in the geometry, mass, and function of the ventricle. In AMI, depending on the magnitude, this event can determine the emergence of acute or chronic cardiac dysfunction such as heart failure. The term reverse cardiac remodeling (RCR) has been used to define the partial reversal of this condition as a response to drug treatment, use of implantable resynchronizers, or more uncertainly, aerobic physical exercise, which have brought about improvement in survival and quality of life (34).

Aerobic physical training has still conflicting results in the scientific literature and it is not clear how it can interfere with ventricular remodeling and contribute to reverse ventricular remodeling. Some studies reported attenuation of ventricular remodeling with physical training (35,36), while others worsened the progression of remodeling (37,38) and others, no relation with remodeling (39,40). Despite the divergent results, it is important to pay attention to the start time of cardiac rehabilitation programs that were not uniform in the studies and the clinical severity after AMI, as well as the level of dysfunction that can be verified by the left ventricular ejection fraction (LVEF).

Observing these possible factors interfering with these results, a systematic review with meta-analysis verified the influence of different times of onset of CR in post-AMI patients with reduced LVEF and observed that better changes in ventricular remodeling and cardiorespiratory capacity with early onset of CR, between 6h and 7 days (acute phase) without an increase in adverse events (41). Despite this, the studies included in the previous review addressed continued CR with a broad outpatient phase, thus, to our knowledge, there are no studies evaluating cardiac morphology immediately after the in-hospital phase as a way to assess the effectiveness of this phase of rehabilitation.

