### **Early CR Protocol – Step 2**

| STEPS | Avaliação Clínica                                            | Tipo de exercício                                                           | Tempo                            | Intensidade  | Dose |
|--------------|---------------------------------------------------------------------|------------------------------------------------------------------------------------|-----------------------------------------|---------------------|-------------|
| 5     | Maintenance of the clinical picture and conditions specified above. | Aerobic: Walking + stair training

Muscular endurance: sitto stand exercise. | 9-15min

2 x 60% test repetitions | Borg 11-12 (3 METs) | 45MET-min   |
| 6     | Maintenance of the clinical picture and conditions specified above. | Aerobic: Walking + stair training

Muscular endurance: sitto stand exercise. | 9-15min

2 x 60% test repetitions | Borg 11-12 (3 METs) | 45MET-min   |

|          |                                                                     |                                                                                    |                                          |                     |           |
|----------|---------------------------------------------------------------------|------------------------------------------------------------------------------------|------------------------------------------|---------------------|-----------|
| 7 | Maintenance of the clinical picture and conditions specified above. | Aerobic: Walking + stair training

Muscular endurance: sitto stand exercise. | 12-20min

3 x 60% test repetitions | Borg 11-12 (3 METs) | 60MET-min |
| 8 | Maintenance of the clinical picture and conditions specified above. | Aerobic: Walking + stair training

Muscular endurance: sitto stand exercise. | 12-20min

3 x 60% test repetitions | Borg 11-12 (3 METs) | 60MET-min |

Subtitle: The frequency of the STEPS is twice a day following the established order. The progression of the exercises focuses on time and intensity variables, following the order of the STEPS. The aim of the protocol is to guarantee 210 MET-min until discharge from the ward and 300 MET-min until hospital discharge, by the sum of the execution dose spent in ICU and ward.

## APPENDIX C - PRESCRIPTION AND FOLLOW-UP FORM FOR EARLY CR Step 3

### Early CR Protocol – Step 3

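### The VO2 and dose objectives and the abstract credit in-hospital CR with effects measured only after a month of home walking given to one arm

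*Protocol*

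**What the plan says.** **What each arm gets.** Under *Early cardiac rehabilitation program*, "all patients in the control and intervention groups, after 8 hours of clinical stability (absence of ischemic signs and symptoms) will perform mobility increment exercises". Randomisation follows once functional mobility is secured. "Both groups will perform steps 1 to STEP 3 of the early CR protocol", with free ambulation and standard drug treatment, but "only the intervention group will proceed to STEP 4 of steps 1 and steps 2 and 3 from early and continued cardiac rehabilitation". Step 3 is the home phase. Intervention patients leave with a booklet "to perform step 3 of semi-supervised and continued cardiac rehabilitation with the exercise time reached at the end of in-hospital rehabilitation", walk five times a week with weekly progression, keep a diary and are telephoned weekly. Appendix C sets out four training weeks.

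**When outcomes are measured.** *Data collection procedures* places the second assessment from day 30 after discharge. The 30CST is done at ICU discharge and 30 days after hospital discharge. HRV is recorded before randomisation and at the 30-day return. Appendix A lists CPET only at the second assessment. *Cardiac morphology* times the follow-up MRIs from 4 weeks and from 3 months after the event. No efficacy measure is scheduled at hospital discharge.

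**What is claimed.** One secondary objective is "To assess the variation in functional capacity by measuring cardiorespiratory fitness after in-hospital CR". Another relates the aerobic dose given in in-hospital CR to functional capacity. The abstract expects in-hospital CR to benefit cardiac structure and function, and through them physical fitness. The primary objective and the MRI and HRV objectives say early CR instead. The programme section defines that as all three steps, home phase included.

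**The concern.** A between-arm difference in VO2 from day 30 reflects everything that differed between the arms up to that day: the STEP 4 and Step 2 sessions in hospital, and then a month of walking with a diary and calls. Nothing in the schedule separates the two parts. If the result is positive, the VO2 objective as worded leads to the report that in-hospital CR raised fitness, although the home phase alone might have produced the difference.

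The dose objective has a further difficulty. By the programme text, home walking starts from the exercise time reached in hospital. Patients with a larger hospital dose will therefore tend to have a larger home dose, and a correlation of hospital dose with VO2 from day 30 will carry both.

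The protocol's rationale is evidence on the hospital phase. Its background notes, for example, that "there are no studies evaluating cardiac morphology immediately after the in-hospital phase". A result credited to the wrong phase would leave that gap open while appearing to fill it.

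**Working it through.** **Inputs.** Appendix B gives minutes, METs and dose for STEPs 1–8, and Appendix C gives the same by week for the home phase. Dose = minutes × METs, times five sessions a week at home.

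**The plan's own figures reproduce.** At the upper time limits:
- Step 1: 5×2 + 10×2 + 15×2 + 15×2 = 10 + 20 + 30 + 30 = 90 MET-min
- Step 2: 15×3 + 15×3 + 20×3 + 20×3 = 45 + 45 + 60 + 60 = 210 MET-min
- Total: 90 + 210 = 300 MET-min

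This matches the stated aim of "210 MET-min until discharge from the ward and 300 MET-min until hospital discharge".

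Home weeks, at the lower time limits: 5×20×3 = 300, 5×25×3 = 375, 5×30×3 = 450, 5×35×3 = 525. These match Appendix C and sum to 1,650 MET-min.

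**What differs between the arms before the day-30 visit.**
- Shared (STEPs 1–3): 10 + 20 + 30 = 60
- Intervention only, in hospital (STEPs 4–8): 30 + 45 + 45 + 60 + 60 = 240
- Intervention only, at home: 1,650
- Home share: 1,650 / (1,650 + 240) = 87.3%
- Sessions on the eight-STEP schedule: 5 extra in hospital and 20 at home

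**Sensitivity of the home share.** Adherence values, and the 60 MET-min for each further hospital session, are assumptions. The programme section allows 8 to 10 hospital sessions, and Borg 9–12 at home, which Appendix B equates with 2 to 3 METs.

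| Case | Home / (home + hospital) | Share |
|---|---|---|
| Upper time limits in both phases | 1,950 / (1,950 + 240) | 89.0% |
| Lower time limits in both phases | 1,650 / (1,650 + 144) | 92.0% |
| Ten hospital sessions (+120) | 1,650 / (1,650 + 360) | 82.1% |
| Home at 2 METs | 1,100 / (1,100 + 240) | 82.1% |
| Ten sessions and 2 METs | 1,100 / (1,100 + 360) | 75.3% |
| 50% home adherence | 825 / (825 + 240) | 77.5% |
| 25% home adherence | 412.5 / (412.5 + 240) | 63.2% |
| Ten sessions, 2 METs and 25% adherence | 275 / (275 + 360) | 43.3% |

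Here 1,950 = 5×3×(25+30+35+40), 1,100 = 5×2×(20+25+30+35), and 144 = 18 + 27 + 27 + 36 + 36. The home share falls below half only when all three unfavourable assumptions are combined.

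**MRI timing.** The baseline scan is in hospital, around day 4 to 6. The first follow-up scan is from 4 weeks after the event, with a two-week tolerance, so between about day 28 and day 42. At the earliest date, at most about 28 − 4 = 24 days of home exercise can have passed; later scans may follow the whole month. The 3-month scan follows all of it. *Data collection procedures* counts its visits from discharge instead (day 30, and day 90 for repeat MRI). The two sections must be reconciled, but under either one the follow-up scans come largely or wholly after home exercise.

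**The case against.** Most of the protocol is worded more carefully than the two objectives. The primary objective and the MRI and HRV objectives concern early CR, and early CR is defined to include the home step. For those, the outcome from day 30 suits the package. A reader might infer that the trial as a whole cannot support its claims. The text does not bear that out: the problem is confined to the VO2 and dose objectives and the abstract's expected result.

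A reader might also infer that the trial claims to test early against late start, since the abstract describes its trial as one "with a CR protocol based on early physical exercise (>8 hours of clinical stability". No objective, outcome or analysis makes that comparison, and the 8-hour criterion only says when the protocol begins. Both arms start then and both perform STEPs 1–3, so nothing about start time is tested. That limits interpretation; it is not a failed objective. The passages on gaps in earlier literature are likewise background.

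Three further points stand. *Statistic Strategy* plans a between-arm test only for CPET; 30CST, MRI and HRV are tested before versus after within each group, although their post values still come largely or wholly after the home phase. The 87% rests on eight hospital sessions, 3 METs and full home adherence, and it leaves out the sit-to-stand work in STEPs 4–8. In-hospital adverse events, recorded session by session in the intervention arm, and the hospital and home doses can still be described.

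None of this makes the in-hospital effect on VO2 identifiable.

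**Conclusion.** The point holds for the VO2 objective, the dose objective and the abstract's expected result. Each attributes to the hospital phase an effect that the schedule cannot separate from a month of home exercise given to one arm only.

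On the printed doses, 87% of the planned intervention-only aerobic dose is home-based. The figure is about 75–82% with ten hospital sessions and/or 2 METs at home, and about 63% at an assumed 25% home adherence. These shares show how much of the contrast lies outside the hospital. They are not shares of effect, and 87% is not a bound. The conclusion does not depend on the exact share, because no outcome is measured between the two phases.

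The comparison of the whole three-step programme is not invalidated.

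**What to change.** Reword the VO2 and dose objectives, the abstract's expected result and the planned conclusion as the effect of the in-hospital STEP 4 and Step 2 sessions plus the one-month semi-supervised home programme, versus STEPs 1–3 and free ambulation. The abstract describes the control arm as usual care with mobilisation guidance, so reconcile it with the programme section first. Report hospital and home dose separately, as description. State that no inference will be made about in-hospital CR alone or about start time. Reconcile the MRI timing in *Cardiac morphology* with *Data collection procedures*.

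Optionally, repeat the 30CST and chest-strap HRV in both arms at hospital discharge and compare the arms there. This would inform those two outcomes only, not VO2 or MRI.

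The core change is wording and alters no exercise prescription. The optional measurement takes minutes per patient with equipment already in use. The price is a narrower claim.
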